### Outcome Measures

Participants will be assessed at baseline (preintervention), postintervention, and 3-month follow-up after they complete the intervention. Assessments will be conducted online via the website [36], where the iABCT will be hosted, and via a telephone interview at pre- and postintervention, except for the 3-month follow-up that will be conducted only via the website. Both participants and researchers will receive email reminders of each assessment time. The study variables and assessment times are summarized in Table 2.

**Table 2 table2:** Study measures, time of assessment, and source of measurement.

Measures	Aim	Assessment point	Assessment source
Admission interview	Screen eligibility criteria (inclusion/exclusion)	Pre^a^	Phone interview
Sociodemographic data	Sex, age, educational level, occupation, and civil status	Pre	Phone interview
M.I.N.I. 7.0.2.^b^	Psychological diagnosis (exclusion criterion)	Pre	Phone interview
Meditation data	Source of learning, frequency, duration of each session (in minutes), lifetime practice (in years), and context of practice	Pre	Phone interview
PHI^c^	Well-being	Pre, post^d^, and FW^e^	Web
SCS-26^f^	Self-compassion	Pre, post, and FW	Web
Compassion scale	Compassion	Pre, post, and FW	Web
FSCRS-SF^g^	Two forms of self-criticism: inadequate self and hated self and the ability to self-reassure	Pre, post, and FW	Web
FFMQ-15^h^	Dispositional mindfulness and mindfulness facets	Pre, post, and FW	Web
RQ^i^	Attachment styles	Pre, post, and FW	Web
GHQ-12^j^	Mental health recent symptoms, feelings, or behaviors	Pre, post, and FW	Web
NAS-7^k^	Nonattachment	Pre, post, and FW	Web
I-PANAS-10-SF^l^	Positive and negative affects	Pre, between modules, post, and FW	Web
PIL-10^m^	General sense of meaning and purpose in life	Pre, post, and FW	Web
Compassion Practice Quality Questionnaire	Difficulties related to the practice of compassion meditation	Between modules, post, and FW	Web
Expectations and Satisfaction Questionnaires	Participants’ expectations before the intervention and their satisfaction after it	Pre and post	Web
UAQ^n^	Usability and acceptability of the internet-based intervention	Post	Web
Qualitative opinion interview	Opinions on the internet intervention, the modules, and unwanted or unexpected effects	Post	Phone call
Attrition rate	Percentage of participants that drop out of the intervention after accessing it for the first time	Post	Web
Patterns of use for each participant	Length of the intervention, time spent on each module, and how many times they enter the modules	Between modules	Web

^a^Pre: preintervention.

^b^M.I.N.I. 7.0.2.: Mini International Neuropsychiatric Interview version 7.0.2 for DSM-5.

^c^PHI: Pemberton Happiness Index.

^d^Post: postintervention.

^e^FW: 3-month follow-up.

^f^SCS-26: Self-Compassion Scale.

^g^FSCRS-SF: Forms of Self-Criticizing/Attacking and Self-Reassuring Scale-Short form.

^h^FFMQ-15: Five Facets of Mindfulness Questionnaire.

^i^RQ: Relationships Questionnaire.

^j^GHQ-12: General Health Questionnaire.

^k^NAS-7: Non-Attachment Scale.

^l^I-PANAS-10-SF: International Positive and Negative Affect Schedule Short Form.

^m^PIL-10: Purpose-In-Life Test.

^n^UAQ: Usability and acceptability Questionnaire.

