### Recruitment

Recruitment will be conducted online using professional and nonprofessional social media (ie, Facebook, LinkedIn, and Twitter), on the website where the internet intervention will be developed and hosted [36], and through advertisements in local newspapers and radios. The study will also be announced in the Master in Mindfulness program at the University of Zaragoza (Spain) and emailed to lists of contacts interested in meditation issues (eg, students on the master’s program and former students, and people subscribing to the newsletter published by the Mindfulness and Compassion Research Group [37]). In addition, posters will be placed in the following locations: Universitat Jaume I, the University of Valencia, the University of Zaragoza (Teruel, Huesca, and Zaragoza campuses), Miguel Servet Hospital (Zaragoza), and the Arrabal Health Centre (Zaragoza). All participants will access the study voluntarily, and no reimbursement for their participation will be provided in any case. The internet intervention aims to promote psychological well-being but not treat any mental disorders or medical conditions.

People who are interested in the study will be asked to contact the research team, and they will be scheduled for an admission telephone interview to screen for the inclusion and exclusion criteria—including a diagnostic telephone interview—and an explanation of the research terms (ie, study design, intervention length, and intervention rationale). Participants meeting the eligibility criteria and giving their informed consent will be allocated to the web-based intervention. A user account and password will be provided via email to each participant for individual use. Baseline assessment will be completed on the website and via a telephone interview before the intervention commences. Participants will be free to withdraw from the intervention or study at any time and without providing justification. In such cases, the research group will endeavor to contact them to ask for reasons and collect data regarding the feasibility of the internet-based intervention developed.

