**Figure 1 figure1:**
[figure not shown]
A screenshot of the “Psicología y Tecnología” (Psychology and Technology) Web platform.

Table 1 presents the contents of each module. In comparison with the original ABCT, the adapted web-based version includes module 0, “Introduction to attachment-based compassion therapy,” to introduce to the participant the basics of the attachment-based compassion model and the program contents. Module 0 also includes tips about the use of formal and informal compassion (when/where/how much/how meditate) and on the importance of progressiveness in compassion training and of home practice between modules. Specific content has been added about “managing guilt” (formal meditation in module 4), “embarrassment” (theoretical component and formal practice in module 5), and “envy” (theoretical component and formal practice into module 7). Moreover, the term, “the figure of affect,” has been replaced by “basic affection” to make it easier to understand and so that participants will not confuse this with “the figure of secure attachment.” Other practices that have been eliminated are “showing forgiveness for the hurt caused by loved ones” (for people with grief experiences) and the “the illusion of labels” because they were not considered relevant for this protocol. Finally, module 8 on equanimity (“Beyond compassion: equanimity”) [6] has not been included in the web-based version because it was considered a different and advanced aspect of compassion.

The length of the interventions will depend on the pace of each participant, who will be advised to complete 1 module per week, taking the days between sessions to complete homework assignments. Each module has been optimized to allow it to be completed in approximately 1 hour. It is estimated that the web-based intervention can be completed in 8 weeks. However, each participant will be free to advance at his/her own pace with a maximum period of 10 weeks. Formal telephone support will not be systematically provided, but participants will be able to make contact for technical assistance (eg, web accessibility problems or forgotten passwords) if necessary.

**Table 1 table1:** Structure and contents of Internet Attachment–Based Compassion Therapy.

Module	Theoretical component	Formal practice	Informal practice

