### Ethics and Dissemination

This trial received approval from the Ethics Committee of Universitat Jaume I (Castellón, Spain; March 6, 2019; file number CD/006/2019) and will be conducted in compliance with the study protocol, the Declaration of Helsinki, and good clinical practice. Data security/confidentially will be guaranteed according to Spanish Organic Law 3/2018 of December 5 on the Protection of Personal Data and Guarantee of Digital Rights; all relevant EU and Spanish privacy laws will be observed and respected. Access will be granted to the internet platform via a unique username-password combination, and all transferred data will be secured using the advanced encryption standard polynomial *m*(*x*)=×8+×4+×3+×+1. Data collected via the website will be stored on secure servers at Universitat Jaume I, with personal data and user-generated data stored in separate databases on different servers. The consent form will be explained and required from all participants by researchers at the initial phone call. Written consent will be obtained before the start of the intervention.

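### The primary outcome (PHI) has one described route after baseline, the login-protected site that also hosts the programme; a back-up route for people who stop using it would be a cheap improvement.

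*Protocol article*

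**What the plan says.** Under Outcome Measures: "Assessments will be conducted online via the website [36], where the iABCT will be hosted". Telephone interviews are added before and after the intervention, "except for the 3-month follow-up that will be conducted only via the website". Table 2 schedules the PHI at "Pre, post^d^, and FW^e" (the raised letters are footnote marks) and gives Web as its only source. The telephone items in that table are screening, the diagnostic interview, sociodemographic and meditation data before the intervention, and the opinion interview after it.

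The site needs an individual login. Recruitment says: "A user account and password will be provided via email to each participant for individual use". Ethics and Dissemination says: "Access will be granted to the internet platform via a unique username-password combination".

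Three measures help to keep people in:
- Outcome Measures: "Both participants and researchers will receive email reminders of each assessment time".
- Recruitment, on people who withdraw: "the research group will endeavor to contact them to ask for reasons and collect data regarding the feasibility of the internet-based intervention developed".
- The section on the intervention: "participants will be able to make contact for technical assistance (eg, web accessibility problems or forgotten passwords) if necessary".

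Outcome Measures times the 3-month assessment from completion of the intervention. The Statistical Analysis Plan section names intention-to-treat and per-protocol analyses, a Little MCAR test, a random-intercept mixed model, and sensitivity analyses with and without imputation, by maximum likelihood and by multiple imputation.

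**The concern.** The channel that delivers the intervention is also the only described channel for the primary outcome. Someone who has stopped using the programme has to log in to the same site to be measured, possibly months later. Whether the PHI is observed may then depend on continued engagement, and engagement may be related to benefit.

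The protocol hypothesises moderate-to-large within-group changes and gains maintained at 3 months (Aims and Hypotheses). It also wants effect sizes for powering a larger trial (Sample Size). If the people who answer are mainly those still engaged, the change from baseline looks larger and better maintained than it is among all those allocated. With one arm, no comparison group would reveal this.

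**Working it through.** **1. Routes to the PHI, by time point**

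| Time point | Web form behind login | Telephone contact | Does the call collect the PHI? |
|---|---|---|---|
| Baseline | Yes | Yes | No |
| Post | Yes | Yes (opinion interview) | No |
| 3 months | Yes | None | Not applicable |

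The PHI has the same single route throughout. What is peculiar to 3 months is that staff have no scheduled call in which a missing form could be noticed and chased.

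**2. What the retention measures reach**

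- Reminders prompt the participant and alert staff, but the form stays behind the same login.
- Contact after withdrawal is for reasons and feasibility data; the PHI is not named. It is described for people who withdraw, and nothing is said of those who simply stop logging in.
- Follow-up is counted from completion, so the article gives a non-completer no due date.

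**3. What the analysis can recover**

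The listed methods rest on data being missing at random given what was observed. They can use a post value when the 3-month value is missing. Someone with a baseline PHI only tells a random-intercept model very little about change. No departure from missing at random is named.

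**4. Illustrative size**

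The protocol states no expected loss, so there is no figure of its own to reproduce. Its minimum of 35 comes from a literature range (24 to 50), without a formula or dropout allowance.

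Let m be the share without a 3-month PHI, and let R and N be the mean changes in responders and non-responders, in SD units. The mean change in all is (1 − m)R + mN, and observed cases show R. The overstatement is therefore R − [(1 − m)R + mN] = m(R − N).

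Inputs:
- m = 11.6%: the dropout rate reported for a web-based compassion trial in the Introduction. It is not a rate of PHI loss in this trial.
- m = 20%, 30%, 40%: assumed.
- R − N = 0.3 to 0.5 SD: assumed.
- For precision, d = 0.5 (assumed, for a moderate effect), with 95% CI half-width 1.96·√(1/n + d²/(2n)).

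| m | Left of 35 | Overstatement, gap 0.3 | Overstatement, gap 0.5 | CI half-width for d |
|---|---|---|---|---|
| 0% | 35 | 0 | 0 | 0.35 |
| 11.6% | 31 | 0.03 | 0.06 | 0.37 |
| 20% | 28 | 0.06 | 0.10 | 0.39 |
| 30% | 24 | 0.09 | 0.15 | 0.42 |
| 40% | 21 | 0.12 | 0.20 | 0.45 |

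Examples: 0.116 × 0.5 = 0.058; 0.4 × 0.5 = 0.20; 35 × 0.6 = 21. These apply to observed cases, before any recovery by modelling.

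**The case against.** The strongest reply has four parts.

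*The article condenses a fuller protocol.* How non-responders are pursued is operational detail that may be written there. This stands as far as it goes: the article supports only the statement that no other route is described, not that none exists. But the website-only rule for 3 months, and Web as the sole source for the PHI, are stated choices rather than silences.

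*The link to disengagement is inferred.* A reader might conclude that those who abandon the programme are the very people whose PHI is lost, with no safety net. The documents do not support that. Recruitment distinguishes leaving the intervention from leaving the study, Table 2 defines attrition as leaving the intervention, an intention-to-treat analysis is planned, and nothing says that an account closes or assessments end when someone stops. Staff as well as participants are reminded, and help with forgotten passwords is offered. Nor is the problem peculiar to 3 months: a telephone call at that visit, modelled on the existing ones, would not recover the PHI unless it asked for it.

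*The size is assumed.* This also stands. At the only dropout rate cited, the overstatement is 0.03 to 0.06 SD, and even the largest figure shown, 0.20 SD, is smaller than the CI half-width of 0.35 at full enrolment. Mixed models and imputation may remove part of it. Still, a wide interval does not excuse an avoidable shift of its centre.

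*This is a feasibility study.* Poor web follow-up would itself be informative, and telephone answers would come mostly from disengaged people, so mode and engagement would be mixed. The first half is met by recording which route yielded each answer. The second is a real limit, and is why results should be shown both ways.

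**Conclusion.** The point holds in a limited form. The PHI at post and 3 months has one described route, the login-protected site that hosts iABCT. Existing calls do not collect it, and the reminders and withdrawal contacts offer no other way to give it. Loss related to disengagement is plausible but not established, and the listed missing-data methods would not test for missingness that depends on unseen values.

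The likely size is small at the cited 11.6% (about 0.03 to 0.06 SD) and reaches 0.20 SD only with an assumed 40% loss and an assumed gap of 0.5 SD, in observed cases. No stated figure in the protocol is wrong, and the design does not contradict itself here. This is a cheap improvement, not an error that invalidates the plan.

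**What to change.** Add to Outcome Measures:

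- The PHI is sought at post and at 3 months from everyone allocated, including those who stopped the programme. State from what date the 3-month assessment is counted for people who do not complete it.
- If the web form is not submitted within 14 days of the reminder, the participant is sent a secure, individual, one-time link to the PHI that needs no platform login.
- If that is unanswered, staff make one short call to collect the PHI.
- The mode is recorded for every answer, and results are reported with and without answers from the back-up route.

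Cost: with 35 enrolled, 11.6% to 40% loss means about 4 to 14 people to pursue per time point (35 × 0.116 ≈ 4; 35 × 0.4 = 14), with fewer calls because the link goes first. Staff who already telephone participants can make them. The link bypasses the access control described under Ethics and Dissemination, so that text needs a matching sentence and the change should be notified as that section provides. The remaining downside is a small number of answers in a different mode, too few to separate mode from engagement. Intervention, endpoint and main model stay as they are.

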### Diagnosis, Screening, Sociodemographic, and Meditation Experience Data

An admission interview will be conducted to screen for inclusion and exclusion criteria. Sociodemographic data of participants will be recorded regarding sex, age, educational level, occupation, and civil status. Variables regarding overall meditation practice will be recorded as follows: any or no meditation experience, source of learning (ie, self-taught, therapy context, teacher or secular training course, and religious context), frequency of meditation (daily, 3 or 4 times a week, once a week or less, 2 or 3 times per month, sporadically, never), duration of each session (mean time in minutes), and lifetime practice (in years), and for participants with experience, the amount of time (in months) of meditation practice interruption and context of practice (secular or religious). Frequency, duration of each session (in minutes), and lifetime practice (in years) will also be asked for different meditation practice types (ie, focused attention meditation, open monitoring meditation, compassion or loving-kindness meditation, values mediation, deconstructive meditations, and informal mindfulness practices). A brief description of each meditation practice will be provided to guarantee the understanding and standardization of the concepts among participants.

Screening for exclusion criteria owing to the diagnosis of a psychological disorder will be performed using the *Mini International Neuropsychiatric Interview* (M.I.N.I. 7.0.2.) [38]. A copyright license for use of the standard M.I.N.I. 7.0.2 in Spanish, based on DSM-5 criteria, will be requested from the authors.

### Feasibility Outcomes

Feasibility outcomes will assess the implementation of iABCT regarding adherence (ie, attrition rate), patterns of use for each participant (eg, length of the intervention, time spent each in each module, how many times they enter the modules), participants’ acceptability (*Expectations and Satisfaction Questionnaires* adapted from Borkovec and Nau [39]), usability (*The Usability and Acceptability Questionnaire* [40,41]), and opinion (qualitative interview).

The *qualitative opinion interview* has been specifically developed to assess participant opinions on the web-based intervention. This semistructured telephone interview includes 14 questions with both quantitative and qualitative open questions: 7 of which refer to the usefulness of the intervention, components, modules, information provided, and multimedia elements (eg, images, audios, videos, PDF files) rated on a scale of 1 to 5 (1=not at all; 2=not very; 3=somewhat; 4=very; 5=extremely) and 2 dichotomous questions (“yes” or “no”) regarding whether they would consider it useful to have the program at their disposal for additional time after completion of the treatment, as well as whether they would like to have longer access. Additionally, interviewers would request to expand on the participants’ qualitative responses for each question. Finally, 2 open questions will be included to assess adverse or unwanted effects and facilitators and barriers to the intervention received.

### Psychological and Mental Health Outcomes

The primary outcome is well-being, which will be assessed using the *Pemberton Happiness Index* [42].

Secondary outcomes include the following: the *Compassion Scale* [43] and the *Self-Compassion Scale* [44] will be used to assess compassion and self-compassion, respectively. Self-criticism will be measured using the *Forms of Self-Criticizing/Attacking and Self-Reassuring Scale-Short form* [45]. Dispositional mindfulness will be assessed using the short *Five Facets of Mindfulness Questionnaire* [46]. The *Relationships Questionnaire* [47,48] will be used to assess attachment styles (ie, secure, preoccupied, dismissive, and fearful). The *General Health Questionnaire* (GHQ-12) [49,50] will be included to measure general mental health status. Nonattachment (eg, I can let go of regrets and feelings of dissatisfaction about the past when pleasant experiences end, I am fine moving on to what comes next) will be assessed using the *Non-Attachment Scale* [51], and positive and negative affects will be measured using the International Positive and Negative Affect Schedule Short Form [52]. The *Purpose-In-Life Test* [53] will assess the general sense of meaning and purpose in life. Difficulties related to the practice of compassion meditation will be assessed using the *Compassion Practice Quality Questionnaire* (adapted from Del Re et al [54]) that has been specifically developed for this study, which includes 10 items that participants score on a scale ranging between 0 and 100, indicating the percentage of the time that their experience reflects each statement.

### Ethics and Dissemination

This trial received approval from the Ethics Committee of Universitat Jaume I (Castellón, Spain; March 6, 2019; file number CD/006/2019) and will be conducted in compliance with the study protocol, the Declaration of Helsinki, and good clinical practice. Data security/confidentially will be guaranteed according to Spanish Organic Law 3/2018 of December 5 on the Protection of Personal Data and Guarantee of Digital Rights; all relevant EU and Spanish privacy laws will be observed and respected. Access will be granted to the internet platform via a unique username-password combination, and all transferred data will be secured using the advanced encryption standard polynomial *m*(*x*)=×8+×4+×3+×+1. Data collected via the website will be stored on secure servers at Universitat Jaume I, with personal data and user-generated data stored in separate databases on different servers. The consent form will be explained and required from all participants by researchers at the initial phone call. Written consent will be obtained before the start of the intervention.

A data monitoring committee (DMC) will be set up, comprising a psychiatrist, the principal investigator, and an independent clinical psychologist familiarized with the administration of internet-based interventions. The DMC will meet 3 times throughout the trial—after the baseline, posttreatment, and at follow-up measurements—but will be available on request at any time to provide support and information to all parties where necessary. The DMC will function independently of the sponsors and funders and will oversee and safeguard all trial participant interests, monitoring the overall conduct of the trial and ensuring the safety of participants by systematically checking negative events and reacting to any extreme distress or risk. In the case of an adverse event emergency, participants will be contacted and encouraged to receive additional help and counseling. Interim analyses are not contemplated in this study, although the DMC could request them if considered necessary for proper conducting of the trial and/or participant safety. Important protocol modifications will be communicated to relevant parties (ie, trial participants, trial registries, journals, ethical committee, and researchers). Results will be disseminated to relevant health care and professional communities and the general population via social media, in peer-reviewed and popular science journals, and at scientific and clinical conferences. Authors of the works derived from this study will be the investigators collaborating in this clinical trial, and there is no intention of using professional writers. A professional native English-speaking editor will check the language and grammar of English written content. Data generated in this trial (ie, full protocol, participant-level data set, and statistical code) will be made available upon reasonable request to the corresponding author.

